### Statistical Analysis

#### Sample Size and Power Analysis

Statistical power was estimated according to the primary outcomes of the project: the change in exposure to inhalable total protein in the breathing zone before T_1_ and after T_2_ and implementing exposure-reducing interventions in the participating salmon processing factories. A previous study in the Norwegian salmon industry reported a geometric mean exposure of total protein in the processing areas of 2.7 (range 0.76-12.62) µg/m^3^ [4]. The study was based on 273 exposure measurements, making it the most extensive study available on assessment of the concentration of total proteins in the salmon processing workers’ breathing zone. The crude data allowed us to estimate the corresponding arithmetic mean exposure of total protein (10.0, SD 5.8 µg/m^3^). Based on these data we estimated that with a significance level of .05 there is a power of 80% of finding a 40%, 30%, and 20% reduction of exposure in 1 intervention arm if we include 34, 59, and 133 measurements in each of the groups, respectively. Since baseline measurements are performed at all sites before intervention, there will be an even higher statistical power given that we can adjust the exposure levels after intervention for mean baseline values at each site. Based on these calculations, we aimed at including 24 workers with 2 repeated measurements in each of the intervention groups (144 measurements in each group equals a total of 432 measurements) both at baseline and after intervention.

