#### Analysis of Data

Detailed description of statistical analyses will be found in the respective scientific publications. In general, for parametric data displaying a normal distribution, results will be presented as arithmetic means with SDs. For data showing a skewed distribution, as is commonly found for exposure measurement data, the results will be presented as geometric means with geometric SDs. Categorical data will be presented as percentages. In case of missing variables, omission or imputation will be performed depending on the type of data.

In general, risk estimates for the various outcomes with 95% CIs will be estimated using a regression model being appropriate for the analysis in question. The estimates will be adjusted for covariates identified as potential confounders, effect modifiers, and mediators. Tests are considered statistically significant at a *P* value of .05.

Analyses related to the intervention study will be performed according to intention-to-treat, regardless of protocol adherence. Results will be reported in line with CONSORT (Consolidated Standards of Reporting Trials) guidelines.

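### The planning mean and SD (10.0, SD 5.8) do not fit the geometric mean and range quoted for the same source data, so the power statement is unsupported as written

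*Protocol article*

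**What the plan says.** Under Sample Size and Power Analysis, the protocol article draws on a previous study in the Norwegian salmon industry. That study "reported a geometric mean exposure of total protein in the processing areas of 2.7 (range 0.76-12.62") µg/m³. On its size the article says: "The study was based on 273 exposure measurements". The next step is: "The crude data allowed us to estimate the corresponding arithmetic mean exposure of total protein (10.0, SD 5.8", in the same units. The text presents the second pair of values as the counterpart of the first. It mentions no different subset, area, unit or exclusion.

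From these data the section concludes that "with a significance level of .05 there is a power of 80" percent. It ties this to three effect sizes and the numbers needed per compared arm: "finding a 40%, 30%, and 20% reduction of exposure in 1 intervention arm if we include 34, 59, and 133 measurements in each of the". The recruitment target is then set on the strength of those calculations: "144 measurements in each group equals a total of 432 measurements", at baseline and again after intervention.

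Under Analysis of Data, the article says of skewed data: "as is commonly found for exposure measurement data, the results will be presented as geometric means with geometric SDs". No geometric SD is given anywhere.

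**The concern.** A geometric mean, a range, an arithmetic mean and an SD from one data set constrain each other. Here the arithmetic mean is 3.7 times the geometric mean (10.0/2.7), which needs a very wide spread. The SD, however, is only 0.58 of the mean, which is a narrow spread, and the largest value quoted is only 12.62. At least one figure is wrong, or the figures describe different things.

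At stake is the justification of the primary outcome's sample size. The three detectable reductions, the 80% power and the target of 144 per group all come from the ratio 5.8/10.0. If that ratio is wrong, the stated power is wrong too, and the documents give no other variance to replace it.

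**Working it through.** **Inputs** (all from Sample Size and Power Analysis): geometric mean (GM) 2.7; range 0.76 to 12.62; mean 10.0; SD 5.8; significance level .05; power 80%; reductions of 40%, 30% and 20%; 144 per group. Sidedness is not stated; two-sided reproduces the plan.

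**1. The plan's own figures.** For two means, n per group = 2(1.96 + 0.8416)² × SD²/Δ², with Δ = 10.0 × reduction.
- 40%: 15.70 × (5.8/4)² = 33.0, rounded up to 34
- 30%: 15.70 × (5.8/3)² = 58.7, rounded up to 59
- 20%: 15.70 × (5.8/2)² = 132.0, rounded up to 133

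All three match (one-sided would give 26, 47 and 104). Only the ratio SD/mean = 0.58 matters.

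**2. Can the inputs coexist if the range is of individual measurements?** These bounds hold for any distribution and any number of measurements.
- *Largest mean given GM and range.* Put all the mass at the two ends. Share at the top: p = ln(2.7/0.76)/ln(12.62/0.76) = 0.451. Mean = 0.76 + 0.451 × 11.86 = **6.11**, below 10.0.
- *Largest SD given mean 10.0 and range.* √[(12.62 − 10.0)(10.0 − 0.76)] = √(2.62 × 9.24) = **4.92**, below 5.8. This does not use the GM.
- *Smallest GM given minimum 0.76, mean 10.0 and SD 5.8, with no upper limit.* Share at 0.76: 33.64/(33.64 + 9.24²) = 0.283; the rest at 10 + 33.64/9.24 = 13.64. GM = exp(0.283 ln 0.76 + 0.717 ln 13.64) = **6.03**, above 2.7.

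**3. If the range is of group or area means.** The bounds lapse, so compare GM, mean and SD under a log-normal.
- GM 2.7 and mean 10.0: σ² = 2 ln(10.0/2.7) = 2.62, geometric SD (GSD) 5.04, SD 35.7, against 5.8 stated.
- Mean 10.0 and SD 5.8: σ² = ln(1 + 0.58²) = 0.29, GSD 1.71, GM 8.65, against 2.7 stated.
- Matching all three with two values needs about a quarter of the data near 0.02 and the rest near 13.4. That is left-skewed, the opposite of ordinary exposure data.

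**4. What the true spread could mean for power.** On the log scale, n per group = 15.70 σ²/[ln(1 − reduction)]², with σ = ln(GSD). The first row assumes a log-normal whose 273 values span the stated range. The expected range of 273 standard normal values is 5.70 (simulated), so σ = ln(12.62/0.76)/5.70 = 0.493, with mean about 3.0, SD about 1.6 and CV about 0.52.

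| Source of spread | GSD | n for 40/30/20% | Power at 144, 20% reduction | Detectable reduction at 144 |
|---|---|---|---|---|
| GM and range | 1.64 | 15/30/77 | 97% | 15% |
| CV 0.58 | 1.71 | 18/36/92 | 94% | 16% |
| Assumed | 2.0 | 29/60/152 | 78% | 20% |
| Assumed | 2.5 | 51/104/265 | 54% | 26% |
| GM 2.7 with mean 10.0 | 5.04 | 158/324/826 | 21% | 41% |

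The last column is 1 − exp(−2.80 σ √(2/144)), for 80% power. All rows treat measurements as independent.

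**The case against.** Several points can be made for the plan.

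- *The ratio may be right even if the values are not.* Sample size depends only on SD/mean. A log-normal fitted to GM 2.7 and the stated range has a CV of about 0.52, close to the planning 0.58 and slightly smaller. On that reading 144 per group is ample. This stands, and it rules out saying that the study is too small.
- *The impossibility is conditional.* The article does not say what the range covers. If it covers area or group means, the strict bounds do not apply. This stands too, but step 3 shows that the three remaining values still clash for right-skewed data.
- *The worst case is the weakest.* GSD 5.04 pairs the GM with the very mean in doubt. It would spread 273 values over roughly 0.03 to 270 and give an SD of 35.7, so it discards both the stated range and the stated SD. This stands. A reader might infer from that row that the trial is several-fold undersized; the documents do not support it.
- *The scale is not settled here.* The sentence on geometric means concerns presentation, and Intervention Outcomes speaks of differences in mean concentration. The model scale and variance components can be left to the statistical analysis plan. This stands, so the scale of the power calculation is not a separate error. At CV 0.58, moving to the log scale lowers n.
- *Baseline is complete.* Recalculation cannot change sampling already done. True, but the power claim is still part of the published justification for the primary outcome.

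**Conclusion.** The concern holds as an inconsistency in the planning inputs. On the plain reading, that the range covers individual measurements, the quoted mean and SD are impossible alongside the quoted GM and range. On the alternative reading they are not credible for skewed exposure data. The stated sample sizes, the 80% power and the 144-per-group target rest on those inputs, so the power statement has no support as written.

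The documents do not determine which figure is wrong, or in which direction the power is off. With 144 independent measurements per group, power for a 20% reduction is 94% to 97% on the spreads best supported by the quoted figures. It falls to 54% at an assumed GSD of 2.5 and to 21% in the poorly supported extreme. Measurements repeated on workers within plants are not independent, so these values are likely to be optimistic.

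Two further readings are tempting but should not be adopted. One is that the study is shown to be underpowered, which depends on a spread that the documents do not establish. The other is that mean and SD were transposed. A log-normal with mean 5.8 and SD 10.0 has GM 2.91, near 2.7, but an SD of 10.0 cannot occur within 0.76 to 12.62 (the maximum is half the range width, 5.93), and nothing in the text says that a swap happened.

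**What to change.** Go back to the crude data of the previous study and recheck the mean, SD, GM, GSD and range. State which measurements each value describes, and whether the range is of individual measurements or of group means. Correct the wrong figures in the sample-size section.

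Then restate, for the sample now fixed, the reduction detectable with 80% power, expressed as a ratio of geometric means on the log scale, since skewed exposure data are to be reported that way. Say whether measurements are treated as independent. The 400 personal protein measurements from T1 could supply the GSD instead, once their quality checks are finished; the Results section still describes them as preliminary.

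The cost is a recalculation from data in hand and a few corrected sentences, with no change to field procedures. The downside is that the restated power may be less favourable than the published claim.

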#### Eligibility and Exclusion Criteria for Individual Participants

All workers employed in, and present at, the processing plants at baseline (T_1_) and follow-up (T_2_) are eligible for answering the self-administered questionnaire. The numbers of invitees for health examinations and individual exposure assessments are limited to a maximum of 99 and 24, respectively, per plant, owing to logistical, financial, and time constraints.

Pregnant participants are excluded from skin prick testing and spirometry, while persons with a history of heart attack or surgical interventions in the eye, stomach, or chest within the preceding 3 months are excluded from carrying out spirometry testing.

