#### Assignment of Intervention

Randomization of intervention arms was not feasible because of different premises of plant infrastructure. The participating plants were therefore allocated to the study arms by the project group, based on meetings and discussion with the local staff and management, and aiming at covering all 3 study arms in each region. Criteria that were taken into account for allocation to a specific arm were prestudy status of awareness and compliance of bioaerosol-reducing behaviors and technical installation, such as use of swabbing; flushing of work areas during work shifts; number, type, and shielding of water nozzles; water pressure; ventilation system; and plans for any alteration of these factors within the study period.

Allocation concealment and blinding was not relevant for obvious reasons.

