## Results

The study was originally planned to begin in fall 2020 but was delayed to September 2021 due to the COVID-19 pandemic. The pandemic further influenced both data gathering and company access due to access restrictions and short-notice sick leaves or quarantines. Among other consequences, this led to delays in baseline measurements, especially in the plants in mid-Norway that had carried out their baseline measurements (T_1_) between March and June 2022, 3 months behind schedule.

As the study is still ongoing and data quality checking is not finished, we only have preliminary results from the baseline measurements at T_1_. The main questionnaire at T_1_ was answered by 740 participants. Due to uncertainties in numbers of distributed questionnaires, it was not possible to calculate a precise response rate, but we estimated its average to be 61% with a range between about 48 (31%) out of 155 and 134 (91%) out of 147. A total of 673 workers participated in the baseline health examinations. Calculating the participation rate is futile, because in several plants there was a much higher number of potential participants than there was capacity to carry out health examinations.

Exposure measurements were undertaken, resulting in over 700 personal measurements (400, 203, and 122 for protein, allergens, and endotoxins, respectively), as well as almost 150 stationary measurements (59, 51, and 34 for protein, allergens, and endotoxins, respectively).

Due to a long time frame of about 2 years between the companies’ original consent to participate in the trial and the actual start of the study, technical adjustments were done in several factories before the study start. Thus, the original plan to allocate 3 plants per intervention group was not feasible. One plant planned adjustments to the ventilation system during the intervention period and was therefore not allocated to any of the original intervention groups at T_0_. This left only 2 groups for the CS arm, while 3 plants each were allocated to the NZ and control group arms.

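### The 80% power figures treat single measurements as independent although whole plants were allocated (3, 3 and 2 per arm), so the 20% target is not supported and the 30% and 40% targets hold only under favourable assumptions

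*Protocol article*

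**What the plan says.** The section on sample size and power takes a mean total protein exposure of 10.0 µg/m³ with SD 5.8 from an earlier study. It claims 80% power at a significance level of .05 for three sizes of effect in one of the intervention arms, namely reductions of 40%, 30% and 20%. The condition attached to this claim is: "if we include 34, 59, and 133 measurements in each of the groups, respectively". It then sets the target: "24 workers with 2 repeated measurements in each of the intervention groups (144 measurements in each group equals a total of 432 measurements"), at each visit. Since 24 × 2 is 48, the 144 must mean 48 in each of three plants, which agrees with the cap on exposure assessment in the eligibility section: "limited to a maximum of 99 and 24, respectively, per plant". The same section adds that adjusting for mean baseline values at each site will raise power further.

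On allocation, Assignment of Intervention says: "The participating plants were therefore allocated to the study arms by the project group". Results reports the outcome: "This left only 2 groups for the CS arm, while 3 plants each were allocated to the NZ and control group arms". The ninth plant is outside the three arms.

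The power section mentions no ICC, design effect, plant effect or within-worker correlation.

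**The concern.** Measurements from one plant share its building, ventilation, production line and measurement week, and each worker was to be measured twice. The article itself describes plants that differ in ways affecting how bioaerosols are generated and removed (Study Setting), places no restriction on concomitant changes (Adherence) and regards stable conditions as unlikely (Strengths and Limitations). The arm effect is replicated over 3 versus 3 plants, or 2 versus 3 for CS, and not over 144 measurements.

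At stake is the power claim for the primary outcome (OM1), on which the recommendation of a measure to the industry is to rest. A null result could be read as a well-powered null when it is not.

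**Working it through.** **Inputs from the article.** Mean 10.0, SD 5.8 (variance 33.64), so reductions of 40/30/20% are 4/3/2 µg/m³; α = .05 (two-sided reproduces the figures, one-sided does not); m = 48 measurements per plant and visit; 3 NZ, 3 control and 2 CS plants.

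**Assumptions.** ICC 0.01 to 0.10, and plant-level T1-T2 correlation r of 0.8 to 0.9. Neither is in the documents. No credit is given for pairing the same worker across visits, and no further loss is taken for two measurements on one worker.

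**The plan's own figures.** n per group = 2(1.96 + 0.84)² × 33.64 / δ² gives 33.0, 58.7 and 132.0 for δ = 4, 3 and 2. Rounded up, these are exactly 34, 59 and 133. One-sided testing would give 26, 47 and 104. No clustering allowance is contained in the figures.

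**Design effect.** DE = 1 + 47 × ICC is 1.47 at 0.01, 3.35 at 0.05 and 5.70 at 0.10. The 144 measurements per arm are then worth 98, 43 and 25. Even without any penalty for few plants, 144 covers the 133 only up to ICC = (144/133 − 1)/47 = 0.0018.

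**Follow-up-only comparison of plant means.** Variance of a plant mean = 33.64 × [ICC + (1 − ICC)/48]. SE² is that variance × (1/3 + 1/3) for NZ versus control, or × (1/2 + 1/3) for CS versus control. Power is from the noncentral t on 8 − 3 = 5 df.

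| ICC | NZ vs control: SE; power for 20/30/40% | CS vs control: SE; power for 20/30/40% |
|---|---|---|
| 0 | 0.68; 65/93/>99% | 0.76; 56/88/98% |
| 0.01 | 0.83; 50/82/97% | 0.93; 42/74/93% |
| 0.05 | 1.25; 26/49/73% | 1.40; 22/41/63% |
| 0.10 | 1.63; 17/32/51% | 1.82; 15/27/43% |

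**Plant change scores (T2 minus T1).** Variance = 2 × 33.64 × [ICC(1 − r) + (1 − ICC)/48], 5 df.

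| ICC, r | NZ vs control: power for 20/30/40% | CS vs control: power for 20/30/40% |
|---|---|---|
| 0.01, 0.9 | 38/69/90% | 31/59/82% |
| 0.01, 0.8 | 36/67/88% | 30/57/81% |
| 0.05, 0.9 | 34/63/85% | 28/54/77% |
| 0.05, 0.8 | 29/55/79% | 24/47/70% |
| 0.10, 0.9 | 30/57/80% | 25/48/71% |
| 0.10, 0.8 | 24/45/68% | 20/38/59% |

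**Adjustment for the plant's baseline mean.** Variance = 33.64 × [ICC(1 − r²) + (1 − ICC)/48]. This is generous, because it ignores sampling error in the baseline mean. For NZ versus control with 8 − 3 − 1 = 4 df, power for 20/30/40% is 57/88/98% at ICC 0.01 and r = 0.9 (the best case), 38/69/89% at 0.05 and 0.8, and 29/54/77% at 0.10 and 0.8. With only the two arms' six plants (3 df), the last two become 33/60/81% and 25/46/68%.

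**Detectable reduction.** 80% power on 5 df needs δ = 3.51 × SE. For ICC 0.01 to 0.10 the follow-up-only comparison detects 29% to 57% (NZ) and 33% to 64% (CS). Over the change-score assumptions the ranges are 35% to 46% and 39% to 52%.

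**A test that ignores plant.** Its true type I error is 2[1 − Φ(1.96 × naive SE / true SE)]. Follow-up only, with naive SE = 5.8 × √(2/144) = 0.68, it is 11% at ICC 0.01 (true SE 0.83) and 41% at 0.10 (true SE 1.63). For the change analysis, dropping the term ICC(1 − r) from the naive variance gives about 6% (0.01, r = 0.9) to 17% (0.10, r = 0.8).

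**The case against.** Four points can be made for the plan.

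- It did not stop at 34 or 59 but aimed at 144 per group. This stands. A reader might infer that no part of the 20-40% claim survives, and the figures do not support that: at ICC 0.01 NZ versus control keeps 82% for 30% and 97% for 40%.
- It foresees baseline adjustment, and OM1 concerns the reduction from T1 to T2, so a follow-up-only calculation is not the intended analysis. This stands too, and is why change-score and baseline-adjusted results are shown. They help at larger ICC when r is high, but a change score does worse than follow-up only at ICC 0.01 (38% against 50% for the 20% target), because sampling error counts twice. Neither restores 80% for 20%.
- The model for OM1 is left open. Analysis of Data promises a regression suited to each question, and Strengths and Limitations mentions repeated and paired sampling. A reader might infer that the trial will test at measurement level with an inflated type I error. The documents do not commit to that, and model detail may sit in an analysis plan not shown. The type I figures are therefore conditional.
- The 3/3/2 split arose after planning. True, but the planned 3/3/3 has the same fault, and the split only adds to it.

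**Conclusion.** The point holds for the power statement. The sizes 34, 59 and 133 are those for independent measurements, and the design allocates plants. Under every assumption examined, the 20% target misses 80%; follow-up only, it reaches just 65% for NZ versus control even at ICC 0. The 30% target is met only at very small ICC: follow-up only, NZ versus control has 82% at 0.01 and CS versus control 74%; change scores do not reach it; and the generous baseline-adjusted calculation reaches it at 0.01 but not at 0.05 with r = 0.8. The 40% target survives only with a small ICC or a high T1-T2 plant correlation. The expectation of still higher power from baseline adjustment does not rescue the 20% claim.

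The size of the loss rests on an ICC and a T1-T2 correlation that the documents do not give. If OM1 were tested ignoring plant, type I error would exceed 5% for any non-zero plant-by-time variance.

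**What to change.** Withdraw the statement of 80% power with 34, 59 and 133 measurements. In its place, give the reduction detectable at plant level for 3, 3 and 2 plants over an assumed range of plant ICC and T1-T2 plant correlation. The T1 data can inform the between-plant and within-worker variances. They cannot inform the plant-by-time variance, since T1 is one week per plant; that must be stated as an assumption.

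Analyse OM1 as arm-by-time change with the plant as unit of inference. Either use a model with plant, plant-by-time and worker effects and small-sample degrees of freedom, or take one change in log geometric mean per plant (8 values, 5 residual df). Report the estimate and confidence interval first.

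The cost is revised wording and a different analysis, with wider intervals and a less favourable stated power. No new data are required.

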**Results:**

Data collection started in September 2021 and was anticipated to be completed by March 2023, but was delayed due to the COVID-19 pandemic. Baseline data from all 9 plants included 673 participants for the health examinations and a total of 869 personal exposure measurements. A total of 740 workers answered the study’s main questionnaire on demographics, job characteristics, lifestyle, health, and health-promoting factors. Follow-up data collection is not completed yet.

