## Methods

### Study Setting and Study Personnel

The study population comprises salmon processing workers from 9 processing plants along the Norwegian coastline, 3 in each of the included geographical areas. The plants are situated in rural areas in western Norway (surrounding area of up to 110 km from Bergen), mid-Norway (up to 190 km from Trondheim) and northern Norway (up to 400 km from Tromsø). The processing plants vary in size, production volume, technology, and number of departments. In some plants the processing line is localized in 1 building, while in other plants the processing steps are separated and localized in several buildings. This can affect both ventilation and other technical solutions which in turn can affect generation and removal of bioaerosols. In some of the factories the processing workers tend to be specialized in specific parts of the processing line (eg, slaughtering, degutting, fileting, and packing), while in others the workers take part in all processes. Shift plans vary in terms of duration of work and breaks. A detailed description of the individual plants, job categories, and tasks will be published in a separate paper.

Study personnel for the fieldwork to gather exposure and health data comprise personnel from the university hospitals and universities of Bergen, Trondheim, and Tromsø. They are competent in occupational hygiene, medicine, nursing, biotechnology, biomedical laboratory science, or sociology, and mainly participate in fieldwork at plants within their own geographical region. Those carrying out health examinations underwent specific training according to study protocols that had been developed within the project group in collaboration with external clinical specialists and in line with national and international guidelines and recommendations. In order to minimize variability in testing techniques, individual study personnel are dedicated to 1 type of health examination whenever possible, and we aim to keep the same personnel within the geographical region and between baseline and follow-up fieldwork.

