#### Exposure Assessment of Bioaerosols

##### Sampling Strategy

Full shift personal exposure measurements of airborne bioaerosols are collected in the workers’ breathing zone at both T_1_ and T_2_. Workers are selected based on their work tasks with the aim of covering different areas of the production process. Within each plant, we aim to include 5 job groups in the exposure assessment: workers from slaughtering, fileting, packing, the laboratory or technical department, and the central control room or administration. For the cross-week measurements, 12 workers carry a backpack with personal measuring equipment on Monday and Thursday containing 3 pumps, each connected to a filter containing a sampling head in the workers’ breathing zone. The filters are analyzed for inhalable protein, inhalable protease enzymes, fish allergens, and endotoxins. On Tuesday and Wednesday, 12 other workers carry 2 pumps whose filters are analyzed for inhalable protein, inhalable protease enzymes, and fish allergens. Workers register work tasks performed while wearing the backpack, in addition to breaks and other time away from the production area.

Stationary exposure measurements for bioaerosols are performed on Tuesday and Wednesday for a minimum of 6 hours during production. Sampling pumps are placed in plastic containers close to one of the following 3 work stations: cutting of gill arches, degutting, and trimming of filets in plants with filet departments. The filters are analyzed for inhalable protein, inhalable protease enzymes, fish allergens, and endotoxins.

Culturable bacteria and fungi are collected using a microbiological air sampler adjusted to sample 100 L and 250 L or 250 L and 500 L of air. This is done on Tuesday in close proximity to the 3 locations in each plant where the stationary bioaerosol measurements are located.

Temperature and relative humidity are registered every 15 minutes in selected areas of the processing plant throughout the week of data collection using direct reading instruments. The instruments are placed centrally in rooms with salmon production, away from sources of heat or cold.

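### The sample-size sentence assigns the per-plant sampling scheme to each intervention group, and the abstract's 869 personal measurements equal personal plus stationary results combined

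*Protocol article*

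**What the plan says.** The sample-size paragraph derives 34, 59 and 133 measurements per group for reductions of 40%, 30% and 20% in inhalable total protein. It then sets the target, which applies to each of the two time points: "24 workers with 2 repeated measurements in each of the intervention groups (144 measurements in each group equals a total of 432 measurements").

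Other sections describe the sampling by plant:

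- The eligibility section says that invitations to health examinations and individual exposure assessments are "limited to a maximum of 99 and 24, respectively, per plant".
- The sampling strategy says "12 workers carry a backpack with personal measuring equipment on Monday and Thursday", and then "On Tuesday and Wednesday, 12 other workers carry 2 pumps".
- The setting section describes "salmon processing workers from 9 processing plants along the Norwegian coastline, 3 in each of the included geographical areas".
- The Results section says that "the original plan to allocate 3 plants per intervention group was not feasible". Three plants went to the nozzle arm, three to control and two to CS. One plant was placed in none of the original arms.

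On the achieved baseline sample, the abstract reports "a total of 869 personal exposure measurements". The Results section reports "over 700 personal measurements (400, 203, and 122 for protein, allergens, and endotoxins, respectively"), and, listed apart from these, 59, 51 and 34 stationary measurements for the same three agents.

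**The concern.** The target sentence contradicts itself. The workers and repeats it gives to a group produce a third of the count it then states for that group. A reader who has only that sentence cannot tell which figure is the target for the primary outcome.

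The unit also decides what happens when an arm loses a plant. A target stated per group appears untouched by the change in allocation. A target stated per plant shows at once that a two-plant arm cannot reach 144.

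The abstract's 869 raises a related problem. Personal protein is the primary outcome (OM 1) and stationary protein is a separate secondary outcome (OM 3). Merging them under the personal label, and adding up several agents measured on the same workers, puts 869 beside a target of 432. It suggests that the target was far exceeded, when the count for the primary outcome is below it.

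**Working it through.** **1. The plan's power figures.** Inputs from the sample-size paragraph: mean 10.0, SD 5.8 µg/m³, significance level .05, power 80%. Sidedness is not stated; two-sided reproduces the figures. With n = 2(1.96 + 0.8416)² x 5.8² / δ²:

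- 40% (δ = 4): 33.0, rounded up to 34
- 30% (δ = 3): 58.7, rounded up to 59
- 20% (δ = 2): 132.0, rounded up to 133

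All three match the plan.

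**2. The target counts.** Inputs: 24 workers per plant (eligibility section; 12 + 12 in the sampling strategy), 2 measurements each, 3 plants per arm as first planned, 9 plants.

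- Per plant: 24 x 2 = 48
- Per arm: 48 x 3 = 144, as stated
- Total: 48 x 9 = 432, as stated

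The totals reproduce exactly when 24 is read per plant. They do not when 24 is read per group.

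**3. The same scheme under the actual allocation.**

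- Nozzle arm and control: 48 x 3 = 144 each
- CS: 48 x 2 = 96
- Eight allocated plants: 144 + 144 + 96 = 384
- Ninth plant: 48, outside the original arms (384 + 48 = 432)

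Power for a 20% reduction (δ = 2), same normal approximation:

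- 144 vs 144: SE = 5.8 x √(1/144 + 1/144) = 0.684; 2/0.684 − 1.96 = 0.97; power 83%
- 96 vs 144: SE = 5.8 x √(1/96 + 1/144) = 0.764; 2/0.764 − 1.96 = 0.66; power about 74%

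**4. The achieved baseline counts (Results section).**

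- Personal: 400 + 203 + 122 = 725
- Stationary: 59 + 51 + 34 = 144
- Sum: 725 + 144 = 869, exactly the abstract's figure
- Overstatement of personal results: 144/725 = 20%
- Personal protein against the nine-plant target: 400/432 = 93%

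The 144 stationary results and the 144 planned per arm are the same number by coincidence.

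**The case against.** The strongest reply is that the design is sound and only its wording slipped. The parenthesis in the target sentence gives the intended totals, and the sampling and eligibility sections confirm them. This stands. A reader might infer from 24 x 2 = 48 that the trial planned 48 measurements per arm and is badly underpowered. The article does not support that: nobody planned 48 per arm, and replacing 144 with 48 would introduce an error. With three plants per arm, the plan's calculation gives 83% power for a 20% reduction.

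A second reply is that the body of the article conceals nothing. It prints the split by agent and calls the results preliminary, and 24 per plant is a maximum. This also stands, so 400 against 432 is not evidence of a failing trial. The misleading figure is confined to the abstract. It has also been argued that 400/3 is about 133, the number needed for a 20% reduction. That average does not describe the arms: the baseline data cover all nine plants, one of which is in no original arm, and CS has two. An even spread, which is an assumption, would give 400/9 = 44.4 per plant, hence about 133 in a three-plant arm and 89 in CS.

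A third reply is that the target sentence records the original aim and should not be rewritten to fit a later allocation. That is right. The 432 target and the 384 that follow from the allocation must be stated apart.

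**Conclusion.** The point holds as a wrong unit and a wrong label.

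- **Target sentence:** 24 workers belong to each plant. The totals 144 per three-plant arm and 432 over nine plants are correct as the original target.
- **Actual allocation:** the two-plant CS arm yields about 96 measurements, below the 133 stated for a 20% reduction. Power is about 74% against a 144-measurement arm. This assumes full recruitment of 24 workers with two measurements each, and treats measurements as independent with no baseline adjustment, as the plan's own calculation does. It still exceeds the 34 and 59 stated for 40% and 30%.
- **Abstract:** 869 overstates personal results by 144 (20%). That stationary results were added in is inferred from the exact match. In any case the abstract and the Results section give different personal totals, 869 and 725. All these counts are analyte results, not separate sampled shifts, and 400 of them carry the primary outcome.

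The finding does not show that the design was mis-sized or that the protein shortfall is serious. It shows that the target and the achieved sample for the primary outcome cannot be read correctly from the sentences meant to state them.

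**What to change.** 1. In the sample-size paragraph, reword the target to: *24 workers at each plant with 2 repeated measurements (48 per plant; 144 per arm with the originally planned 3 plants; 432 in total)*, at each time point.
2. Add a separate sentence on the actual allocation: 144 in the nozzle and control arms, about 96 in CS, 384 over the eight allocated plants, and one plant outside the original arms. Note that 96 is below the 133 given for a 20% reduction.
3. In the abstract, replace the 869 with: *725 personal and 144 stationary analyte results, including 400 personal protein measurements (432 planned over 9 plants)*.
4. Report the baseline personal protein count by arm, with the unallocated plant shown separately.

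The cost is two corrected sentences, one added sentence and one tabulation of data already held. No change to design, sampling or analysis is needed. If the article can no longer be amended, the same statements belong in the report of the intervention results.
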